### Concomitant therapy

2.6

All PSD patients will receive guideline-based pharmacotherapy and swallowing rehabilitation per institutional practice (15, 16).

Swallowing rehabilitation protocol: Indirect training will include lip-closure exercises, mandibular movement training, lingual mobility exercises, cold stimulation, articulation training, vocal cord adduction training, cough training, and stimulation to facilitate the swallowing reflex. Direct training will include positioning the patient in a seated posture or at a 30° reclined angle with the neck flexed forward. For patients with hemiplegia, elevate the affected side of the shoulder and back. Select appropriate foods based on the patient's specific condition and dietary habits. Start with small portions (1–4 ml) and gradually increase the amount. The feeding speed will be modified as needed, and techniques including dry swallowing, alternating swallowing, nodding swallowing, and lateral swallowing will be used to eliminate and swallow food remaining in both pyriform sinuses.

Swallowing training should be performed once daily for 30 min, five times weekly, for a total of 6 weeks of treatment.

To ensure consistency across participants, all therapists will follow a standardized rehabilitation procedure for dysphagia. Prior to trial initiation, therapists will receive unified training. Adherence to the rehabilitation protocol will be recorded in CRFs and monitored by the Data Monitoring Committee.

Throughout the entire trial, participants in both groups will not be permitted to receive any additional targeted therapies for dysphagia. If concomitant prescription medications are required, all relevant details will be documented in participants' case report forms (CRFs). These data will be independently reviewed by two blinded investigators.

### Outcomes and assessment schedule

2.7

#### Neuroimaging methods

2.7.1

MRI data acquisition: Rs-fMRI and DTI data will be acquired using a 3.0-T MRI system equipped with a 48-channel head coil (SIGNA Premier; GE Healthcare, Milwaukee, USA). Resting-state BOLD fMRI will use a two-dimensional gradient-echo echo-planar imaging (EPI) protocol, which has a multi-band (MB) factor of 2 and a parallel imaging factor of 2. The imaging parameters are as follows: repetition time (TR) = 2,000 ms, echo time (TE) = 30 ms, field of view (FOV) =224 mm, flip angle = 90°, matrix size = 64 × 64, in-plane voxel size = 3.5 × 3.5 mm^2^, slice thickness = 3.5 mm (no gap), comprising 43 axial slices with an interleaved acquisition order. Automated shimming and phase correction will be enabled. The total scan duration will be approximately 8 minutes, yielding 240 volumes. Subjects will be required to remain still with eyes closed, avoiding movement and falling asleep.

DTI acquisition: The DTI protocol will employ an axial spin-echo EPI sequence, b-value 1,000 s/mm^2^, comprising 35 non-collinear diffusion directions alongside one b0 image per repetition. The imaging parameters will be: TR = 5714 ms, TE = minimum (vendor-optimized), FOV = 224 mm, matrix size = 112 × 112, Isotropic voxel size = 2.0 × 2.0 × 2.0 mm^3^, and 76 axial slices covering the entire brain. The multiband factor will be 2, with fat saturation enabled, phase encoding in the right-left direction, and a number of excitations (NEX) of 2 for diffusion. Susceptibility and eddy-current correction will be executed during preprocessing.

Structural MRI: A 3D sagittal T1-weighted magnetization-prepared rapid acquisition gradient-echo (MPRAGE) will be taken for anatomic reference, segmentation, and cortical thickness and volume analyses, with parameters including: FOV = 256 mm, matrix size = 256 × 256, isotropic resolution = 1 mm^3^, 192 slices, flip angle = 8°, TE = 3.0 ms, TR = 7.3 ms, and inversion time (TI) = 1,321 ms. Furthermore, 3D sagittal T2 weighted and T2 fluid attenuated inversion recovery (FLAIR) (both 1 mm isotropic resolution) will be used for lesion delineation and quality control.

#### Primary outcome

2.7.2

Derived imaging metrics will be calculated from the acquired rs-fMRI and DTI data as described below. The primary neuroimaging outcomes are defined as the changes from baseline to week 6 in prespecified rs-fMRI metrics (ALFF, ReHo, and FC) and DTI metrics (FA and MD). In addition, 20 healthy controls will undergo baseline rs-fMRI and DTI examinations to provide a reference for PSD-specific neuroimaging alterations.

Rs-fMRI: Rs-fMRI is extensively utilized to probe the neural mechanisms of PSD. The rs-fMRI markers include amplitude of low-frequency fluctuations (ALFF), regional homogeneity (ReHo), and functional connectivity (FC), which can be used to reflect brain function in patients with PSD. However, existing research primarily emphasizes activation in localized brain regions, with insufficient exploration of acupuncture's effect on functional networks in PSD patients (17).

Therefore, we employed rs-fMRI to analyze brain functional network connectivity, aiming to further clarify the central mechanisms underlying acupuncture treatment for PSD.

ALFF: ALFF reflects the local activity level of specific brain regions by calculating signal strength in the 0.01–0.1 Hz frequency band. It is commonly utilized to explore activation patterns in various brain areas, facilitating our understanding of functional changes across different regions following a stroke, particularly those related to swallowing (18).ReHo: ReHo can capture local coherence changes within swallowing-network nodes (e.g., insula, M1, SMA) in PSD by measuring the temporal synchrony between a given brain region and its adjacent voxels, thereby assessing the consistency of neuronal activity within that region (19).FC: Functional connectivity assesses the interconnections between brain regions based on correlations in temporal sequences. Seed-based analysis (e.g., bilateral insula, M1 orofacial area, SMA) and independent component analysis (ICA) employ data-driven methods to capture broader network-level modulation. Evaluating overall connectivity patterns enhances our understanding of how acupuncture may improve neural network function in PSD patients (20, 21).

DTI: DTI facilitates the reconstruction, visualization, and quantification of structural and fiber connectivity within the brain (22). Fractional anisotropy (FA) serves as an index of the integrity of white matter microstructure, while mean diffusivity (MD) is indicative of pathology, including edema and necrosis (23). Consequently, DTI provides essential insights into structural remodeling and fiber tract reorganization in patients with PSD (24).

By integrating rs-fMRI and DTI through multimodal analysis, both functional and structural connectivity within the brain can be simultaneously examined. This approach provides more comprehensive information on neural networks and may help elucidate the structural-functional coupling mechanisms underlying acupuncture-mediated recovery of swallowing function. This contributes to a deeper understanding of the multidimensional mechanisms underlying acupuncture-induced neural reorganization in patients with PSD.

#### Secondary outcomes: mean changes in SSA, VFSS-based measures (MBSImP and PAS), MoCA, and SWAL-QOL scores during the study period

2.7.3

(1) SSA (Standardized Swallowing Assessment): The SSA consists of three components: clinical examination, 5 ml and 60 ml water swallowing tests (25). Higher scores reflect more severe swallowing dysfunction. Existing evidence suggests that the SSA offers good sensitivity and specificity when used to assess PSD patients (26).

(2) VFSS (Video fluoroscopic Swallowing Study)-based measures: VFSS is considered one of the most accurate methods for the diagnosis of dysphagia and is conducted using X-ray fluoroscopy to evaluate the transit of food boluses with contrast agent from the oral cavity to the esophagus in both anteroposterior and lateral views (27). Swallowing impairment will be quantified using the Modified Barium Swallow Impairment Profile (MBSImP), which scores standardized physiologic components observed on VFSS across the oral and pharyngeal phases, including pharyngoesophageal segment opening, and also incorporates upright esophageal clearance as a screening component, using ordinal impairment ratings (0 = normal; higher scores = more severe impairment), thereby generating a profile-based characterization of swallowing dysfunction (28). Because airway invasion is a critical safety dimension, penetration/aspiration events during VFSS will additionally be graded using the Penetration–Aspiration Scale (PAS), an 8-point ordinal scale in which PAS = 1 indicates no airway entry and higher scores indicate increasing penetration/aspiration severity (29). MBSImP (with PAS as a complementary safety indicator), together with SSA, will enable a comprehensive evaluation of swallowing function and therapeutic response in PSD.

(3) MoCA (Montreal Cognitive Assessment): In traditional Chinese medicine, “Spirit” refers to the sum of vital activities and mental processes, including cognition, perception, and emotion. Cognitive function is therefore considered part of “Spirit” and reflects its regulatory capacity, which also influences cerebral function (30). Patients with PSD frequently present with concomitant cognitive impairment (31). The MoCA serves as a widely adopted tool for cognitive evaluation with strong reliability and validity (32). It assesses eight domains: attention, orientation, fluency, naming, visuospatial skills, abstraction, delayed recall, and sentence repetition. The total score is 30, with one additional point added for individuals with fewer than 12 years of education. A lower score indicates greater cognitive impairment. It will be used to quantify changes in cognitive function attributable to acupuncture.

(4) SWAL-QOL (Swallowing Quality-of-Life Questionnaire): The SWAL-QOL comprises 44 items covering appetite, mealtime duration, food selection, sleep, and psychological status, and is specifically developed to measure the quality of life of individuals with PSD (33). A higher score corresponds to better quality of life. It will be employed to evaluate the impact of acupuncture on patients' quality of life.

Assessment schedule: baseline (week 0), weeks 2 and 4, and week 6 (end-of-treatment). All assessments will be performed by trained, blinded evaluators.

### Quality control (QC) & exclusion rules

2.8

Head Motion (rs-fMRI): Frames exhibiting a framewise displacement (FD) greater than 0.5 mm will be scrubbed; datasets with an average FD > 0.2 mm or containing more than 20% high-motion frames will be flagged for exclusion or sensitivity analyses. Summary statistics and outlier count for FD and DVARS will be reported (34, 35).

Image Integrity: Visual quality control will assess co-registration and normalization accuracy, field-of-view coverage, and the presence of artifacts (e.g., ghosting, spikes) (36).

DTI Artifacts: Automatic detection and removal of corrupted directions or slices will be implemented, alongside a review for residual distortion post-TOPUP and EDDY correction (37).

Reproducibility: All parameters, masks, and scripts will be version-controlled (38).

### Sample size

2.9

This study is designed as an exploratory, mechanism-oriented neuroimaging trial. At present, there are limited prior data from sham-controlled acupuncture studies in post-stroke dysphagia that combine multimodal MRI outcomes with comparable clinical endpoints, which makes a formal power calculation based on a single anticipated effect size difficult. Therefore, the planned sample size was determined with reference to previous neuroimaging studies, practical feasibility, and the exploratory nature of the present protocol. Given the characteristics and high costs associated with neuroimaging studies, sample sizes are generally smaller compared with conventional clinical trials, and there is currently no standardized consensus regarding the minimum sample size required to achieve stable statistical power. A study in 2002 reported that a sample size of 12 subjects was sufficient to provide relatively stable statistical power in rs-fMRI research (39). In 2007, another study using auditory stimulation of rs-fMRI suggested that a sample size of 13–15 subjects was adequate for stable statistical inference (40). In 2011, investigators compared sample sizes of 5, 8, 14, 17, and 21 subjects under otherwise consistent conditions. They observed that smaller sample sizes (e.g., 5 or 8) produced fewer activation regions with greater variability, whereas larger sample sizes yielded more activation clusters and reduced intergroup differences (41). Ultimately, the literature recommends that, where ethically and practically feasible, neuroimaging trials should include at least 20 subjects per group (42).

Taking into account the constraints of study duration, patient hospitalization time, and available manpower, and with reference to previous clinical research, we determined that a randomized controlled trial with 20 participants per group (40 in total) would be appropriate. Considering an expected 15% dropout rate, the final planned sample size is 46 participants [40 × (1 + 15%) = 46].

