### Registration and trial design

2.1

This single-blind, randomized, sham-controlled trial aims to investigate the therapeutic efficacy and neural mechanisms of Tiao Shen Li Yan acupuncture in patients with PSD.

Forty-six participants will be randomized in a 1:1 ratio to receive Tiao Shen Li Yan acupuncture or sham acupuncture. An additional cohort of healthy volunteers will undergo baseline rs-fMRI and DTI for reference comparisons. Participants will be included only if they fulfill all eligibility criteria and submit written informed consent. Figure 1 shows the research process for this article.

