### Randomization and blinding

2.4

Randomization will be performed using simple randomization with a random number table. Randomization codes will be sealed in opaque, sequentially numbered envelopes, each containing the corresponding allocation card. Eligible participants will be enrolled in chronological order, and the envelopes will be opened sequentially. A study coordinator will assign participant identification codes and record them in the case report forms. The treating acupuncturists will open the envelopes in sequence and allocate participants accordingly. Baseline details (including name, sex, age, and enrollment date) will be recorded prior to randomization. Opened envelopes will be stored securely in a locked cabinet.

Given the nature of acupuncture, blinding of the acupuncturists cannot be fully implemented. However, outcome assessors, imaging analysts, data managers, and statisticians will remain blinded to allocation in order to minimize potential bias. Blinding procedures will be monitored by the institutional ethics committee. Unblinding will occur only after database lock and completion of primary analyses.

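### The 15% dropout allowance is added to 40 instead of dividing by 0.85, so 46 randomized gives about 39 expected completers and narrowly misses the stated 20 per group

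*Protocol article*

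**What the plan says.** Section 2.9 (Sample size) explains that the lack of comparable data "makes a formal power calculation based on a single anticipated effect size difficult". It reviews earlier imaging studies and ends with a literature recommendation, qualified by ethical and practical feasibility, that "neuroimaging trials should include at least 20 subjects per group". Weighing study duration, hospital stay and staffing as well, the authors conclude: "we determined that a randomized controlled trial with 20 participants per group (40 in total) would be appropriate". The allowance for loss follows: "Considering an expected 15% dropout rate, the final planned sample size is 46 participants", with the formula 40 × (1 + 15%) = 46 in brackets.

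Two other sections bear on how many patients each arm will have:
- **Allocation.** Section 2.1 says: "Forty-six participants will be randomized in a 1:1 ratio to receive Tiao Shen Li Yan acupuncture or sham acupuncture". Section 2.4 gives the method: "Randomization will be performed using simple randomization with a random number table". No blocks, strata or fixed arm totals are described.
- **Usable scans.** Under section 2.8, rs-fMRI "datasets with an average FD > 0.2 mm or containing more than 20% high-motion frames will be flagged for exclusion or sensitivity analyses". No expected rate of such datasets is given.

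**The concern.** The 15% is a share of the patients who are randomized. Adding 15% of the target to the target covers a loss of 15% of 40, which is 6 patients. A loss of 15% of 46 is 6.9 patients. The allowance is therefore slightly too small for the dropout rate that the plan itself expects, and the formula is printed, so the slip is in the text and not in a detail left to another document.

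At stake is whether the sample-size section describes correctly what the design will yield. A reader would take it that 46 randomized is expected to leave 20 per group. It is expected to leave slightly fewer. Simple randomization adds to this, because it does not hold the arms at 23 each.

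**Working it through.** **Inputs.** Target 20 per group, 40 in total (2.9). Dropout 15% (2.9). Planned total 46 (2.1 and 2.9). Allocation 1:1 by simple randomization (2.1 and 2.4).

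**1. Reproduce the plan's figure.** n × (1 + d) = 40 × 1.15 = 46.0. This matches exactly.

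**2. What 46 delivers at 15% dropout.** N × (1 − d) = 46 × 0.85 = 39.1 in total, and 23 × 0.85 = 19.55 per arm. The shortfall is 40 − 39.1 = 0.9.

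**3. Loss that 46 can absorb.** 1 − 40/46 = 6/46 = 13.0%.

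**4. Inflation that meets the target in expectation.** n/(1 − d) = 40/0.85 = 47.06. Per arm, 20/0.85 = 23.53, so 24 per arm and 48 in total. Check: 48 × 0.85 = 40.8, or 20.4 per arm.

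**5. What the shortfall costs.** With equal arms, the standard error of a group difference is proportional to √(2/n). Moving from 20 to 19.55 per arm multiplies it by √(20/19.55) = 1.011, an increase of about 1%.

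**6. What simple randomization adds.** If each of 46 patients is assigned independently at 50:50, arm size is Binomial(46, 0.5).
- P(exactly 23/23) = 11.7%.
- P(one arm below 20 before any dropout) = 30.2%. With 48 patients this is still 19.3%.

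**7. Precision cost of imbalance.** The standard error is proportional to √(1/n₁ + 1/n₂).
- 23/23: √(2/23) = 0.2949.
- 19/27: √(1/19 + 1/27) = 0.2994, about 1.5% larger.
- 16/30: √(1/16 + 1/30) = 0.3096, about 5% larger.

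**8. Chance that both arms end with at least 20 completers**, assuming independent 15% dropout in each arm.

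| Design | Probability |
|---|---|
| 46, simple randomization | 11.9% |
| 46, fixed 23/23 | 29.1% |
| 48, simple randomization | 24.6% |
| 48, fixed 24/24 | 50.9% |

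The last row shows what a correct inflation does. It meets the target on average and does not guarantee it in every realization.

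**The case against.** The strongest reply is that the error has almost no consequence. It amounts to 0.9 of a completer. Section 2.9 calls the trial exploratory and states no power or effect size that 46 fails to support. The Discussion already lists the small sample as a limitation. All of this stands, and it makes the point minor. It does not make the formula right.

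The documents do not support several stronger readings that a reader might infer:
- **That 20 per group is the only basis for the size.** Section 2.9 also cites feasibility, the exploratory aim and earlier studies, some of which found 12 to 15 subjects adequate. It says that no consensus minimum exists. The 20 is a soft benchmark.
- **That the plan claims 46 guarantees 20 completers per arm.** It calls 20 per group appropriate and 46 the planned size, and goes no further. The 11.9% in the working therefore does not show a broken promise. Even 48 split exactly 24/24 meets that strict criterion only about half the time.
- **That simple randomization is an error.** It is a legitimate method, and the imbalance it is likely to produce costs little precision. Blocking has its own drawback here: the treating acupuncturists, who are not blinded, open the envelopes at a single site, and such a setting makes blocks easier to guess.
- **That motion control will shrink the sample by a known amount.** Section 2.8 says that such datasets "will be flagged for exclusion or sensitivity analyses", so exclusion is not automatic. The motion rule covers rs-fMRI and not the FA and MD outcomes. No failure rate is given, so no reduced total can be derived.

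**Conclusion.** The inflation formula in 2.9 is wrong as written. Under the plan's own 15% dropout, 46 randomized gives 39.1 expected completers (19.55 per arm) against a stated 40 (20 per arm). The correct figure for that target is 48. This part rests only on numbers printed in the protocol and on dropout meaning a proportion of those randomized.

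Separately, 1:1 under simple randomization is an expected ratio, with about a 30% chance that one of the arms starts below 20. That figure assumes independent 50:50 assignment. It would not apply if the list was in fact restricted, but then 2.4 would need correcting.

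Severity is minor: two patients on the planned size, about 1% on the standard error, and no stated power lost.

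**What to change.** **Required, in 2.9.** Replace the formula with 40/(1 − 0.15) = 47.06 and choose one of two statements:
- Keep 46, and say that at 15% dropout about 39 completers are expected, 19 to 20 per arm.
- Keep the target of 40 completers, and plan 48 (24 per arm).

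In either case, add one sentence that usable rs-fMRI datasets may be fewer after the motion checks in 2.8, and one that simple randomization (2.4) makes 1:1 an expected ratio, with about a 30% chance at 46 that one arm starts below 20.

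**Cost.** The first option is a change of text and a slightly less favourable figure. The second means two more patients, an amendment, and the new number wherever 46 appears (Abstract, 2.1, 2.9 and the limitations in the Discussion). It is open only if recruitment is, and section 2.15 planned recruitment to end on 31 December 2025.

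**Optional.** If allocations remain, concealed blocks of randomly varying size would limit further imbalance. They cannot undo imbalance already present, would need an amendment and a new list for the remaining envelopes, and carry the predictability risk noted above. The correction does not depend on them.

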### Data collection

2.10

Data collection will be performed by therapists employing standardized CRFs. Two independent researchers will then enter the data into a secure database. All analyses will be conducted under the supervision of an independent data monitor to ensure accuracy, consistency, and data integrity. For participants who withdraw, their number and reasons (particularly those related to AEs) will be carefully documented.

### Statistical analysis

2.11

#### fMRI data analysis

2.11.1

Preprocessing and analyses will be conducted with SPM12, DPABI, and FSL. Functional and structural connectivity will be analyzed using independent component analysis (ICA) and canonical correlation analysis (CCA) (43–45). ROI-based analyses will prioritize prespecified swallowing-related hubs (the insula, basal ganglia, frontal cortex, M1, SMA, corona radiata, and S1) as the primary ROI set for functional and structural connectivity tests. Network-level extensions (e.g., the default mode network (DMN), the frontal-temporal-sensory-motor circuit, the sensory-motor-insular-thalamic circuit and the insula-cerebellum-occipital circuit) will be reported as secondary/supportive analyses with appropriate multiple-comparison control. Structure–function coupling will be assessed by examining the relationship between functional connectivity and structural connectivity between corresponding brain regions. Functional connectivity (FC) will be calculated as the Pearson correlation between the BOLD time series of predefined regions of interest (ROIs). Structural connectivity will be derived from diffusion tensor imaging using probabilistic tractography to identify white-matter fiber tracts connecting the same ROI pairs. For each tract, the mean fractional anisotropy (FA) along the reconstructed fibers will be calculated to represent the integrity of the structural pathway. Structure–function coupling will then be evaluated by assessing the relationship between FC strength and tract-specific FA values across ROI pairs (46). In addition to the hypothesis-driven ROI analyses, exploratory whole-brain analyses will be conducted to identify potential PSD-related brain regions beyond the predefined swallowing network. Voxel-wise comparisons of rs-fMRI metrics (e.g., ALFF and ReHo) will be performed across the whole brain between groups. Statistical analyses will be conducted using a general linear model framework, and multiple comparisons will be controlled using false discovery rate (FDR) correction (p < 0.05). This will allow us to assess how acupuncture modulates the interaction between structural integrity and functional network organization in PSD.

To correct for multiple comparisons, we will apply the false discovery rate (FDR) at the voxel level and Bonferroni correction for network-level metric (47).

Statistical Modeling: For clinical outcomes and imaging metrics, linear mixed-effects models will be employed to assess within-subject change (baseline vs. week 6) and between-group differences (acupuncture vs. control), while adjusting for sex, age, stroke severity, and lesion volume (48). Correlation analyses will test associations between rs-fMRI/DTI metrics and clinical improvement in swallowing function (SSA/VFSS-based measures/MoCA/SWAL-QOL scales) (49, 50). This will aid in assessing whether alterations in brain networks correlate with improvements in swallowing function, thereby enhancing the clinical interpretability of imaging findings. Depending on the assumptions of normality and linearity, analyses will use either Pearson's correlation coefficient or Spearman's rank correlation coefficient.

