Post-stroke dysphagia (PSD) occurs when cerebral infarction disrupts the distributed neural system that supports swallowing, leading to abnormalities in both network connectivity and white-matter integrity. Importantly, converging neuroimaging evidence suggests that PSD is best conceptualized as a network-level disorder rather than a focal lesion effect, involving coordinated dysfunction across cortical and subcortical hubs. At the cortical level, swallowing-related control engages the sensorimotor cortex (M1/S1/S2), SMA, and frontal regions (including IFG), and interacts closely with subcortical structures such as the thalamus, insula, and basal ganglia, as well as bottleneck white-matter regions (e.g., corona radiata/internal capsule) (55). Recent work has further described modular organization within the swallowing connectome (e.g., insula, cerebellum, sensorimotor–cingulate, IFG–S2–corpus callosum–basal ganglia–thalamus, and premotor–posterior parietal modules), which can be arranged into higher-order circuits supporting swallowing control and compensation (55). Notably, prior rs-fMRI studies in PSD have reported both regional activity alterations and connectivity abnormalities across these hubs, including the sensorimotor cortex, insula, cerebellum, cingulate, thalamus, and basal ganglia (56). Across studies, the most frequently implicated loci include the insula, basal ganglia, frontal cortex, M1, SMA, corona radiata, and S1(57). However, brain network–level evidence remains limited, and existing studies have only partially examined how these regions reorganize as integrated circuits during recovery. For example, rs-fMRI and fNIRS studies suggest abnormalities in DMN and reduced connectivity between the frontal–temporal–sensory–motor circuit and the sensory–motor–insular–thalamic circuit; moreover, altered insula–cerebellum–occipital functional connectivity has been associated with dysphagia severity (51, 58).

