Therefore, in the present study we explicitly separate primary and secondary analyses. The primary (confirmatory) analyses anchor structure-function coupling tests to a prespecified ROI set that captures core swallowing-related hubs with consistent PSD abnormalities (insula, basal ganglia, frontal cortex, M1, SMA, corona radiata, and S1). The secondary (supportive) analyses extend to larger-scale circuits (DMN, frontal–temporal–sensory–motor, sensory–motor–insular–thalamic, and insula–cerebellum–occipital circuits) and are interpreted as hypothesis-generating.

DTI provides complementary insight into the microstructural substrates of PSD. The severity of white-matter injury—reflected by FA and MD metrics—is closely related to the severity of dysphagia, and adaptive white-matter changes may accompany recovery (59). Stroke is associated with disturbances of both functional and structural networks and with state-dependent reductions in functional-structural coupling (60). Therefore, this study included 20 healthy controls as a baseline reference to identify network sites with PSD abnormalities. Combined rs-fMRI and DTI analyses of SC-FC coupling sensitively index clinical impairment and recovery after PSD (46, 60).

Rs-fMRI studies indicate that acupuncture can activate swallowing-related cortical regions in PSD and enhance activity within central swallowing hubs, thereby promoting functional recovery of the cortical swallowing centers. FNIRS evidence suggests that acupuncture facilitates frontotemporal-sensorimotor network integration (61). However, PSD involves not only widespread cortico-cortical injury but also disruption of cortico-subcortical networks, and the mechanisms of structure-function reorganization remain insufficiently understood (51).

Building on this analysis hierarchy, we will examine whether acupuncture-related changes in structure-function coupling and circuit-level functional connectivity track clinical improvement over the 6-week intervention period, using healthy controls as a baseline reference.

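### The primary ROI set uses the corona radiata, a white-matter region, as a node for BOLD connectivity and tractography, so over a quarter of its pairs cannot be read as hub-to-hub connectivity

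*Protocol article*

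**What the plan says.** Section 2.11.1 (fMRI data analysis) of the protocol article names one list and assigns it to the FC tests and the structural tests alike: "ROI-based analyses will prioritize prespecified swallowing-related hubs (the insula, basal ganglia, frontal cortex, M1, SMA, corona radiata, and S1) as the primary ROI set". The same section then fixes how each quantity is obtained from that list.

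- Functional: "Functional connectivity (FC) will be calculated as the Pearson correlation between the BOLD time series of predefined regions of interest (ROIs").
- Structural: the plan is "using probabilistic tractography to identify white-matter fiber tracts connecting the same ROI pairs", after which FA is averaged along each tract.
- Coupling: FC strength is related to tract FA over the ROI pairs. No pair is excluded.

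The Discussion repeats the seven regions and raises their status: "The primary (confirmatory) analyses anchor structure-function coupling tests to a prespecified ROI set that captures core swallowing-related hubs". A little before that, when it describes the anatomy of swallowing control, it names cortical and subcortical structures "as well as bottleneck white-matter regions (e.g., corona radiata/internal capsule"). So the article itself classes the corona radiata as white matter. Neither section says that the corona radiata serves only the FA and MD measures.

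**The concern.** FC and structural connectivity need different things from a node. For FC, a node should be a region whose BOLD signal stands for the activity of a hub. For tractography between two nodes, each should be an end of the pathway and not a stretch of it. The corona radiata, on the article's own description, is a white-matter passage. Used as a node it has two faults.

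1. Its BOLD correlation with the insula or M1 can be computed, but it is not a measure of connectivity between two swallowing hubs.
2. A tract that ends in the corona radiata has part of its length in the node, so the pair's FA is partly a measurement of the node.

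Because coupling is assessed across pairs, these entries affect the whole index and not only their own cells. They are also linked: every one of them depends on the same piece of tissue. The Discussion places the corona radiata among the sites most often found abnormal in PSD. Local damage or oedema there could therefore move all of these pairs together and be read as a change in coupling. The model in 2.11.1 adjusts for lesion volume, not for where the lesion lies.

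**Working it through.** The article states no number of nodes or pairs, so there is no figure of its own to reproduce. The check is a count.

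**Inputs**
- Seven named regions (2.11.1, repeated in the Discussion): insula, basal ganglia, frontal cortex, M1, SMA, corona radiata, S1.
- Assumption A: every pair is used, since no exclusion is stated.
- Assumption B: the node count. Laterality is not given for this set. The seed examples in 2.7.2 mention a bilateral insula, so both merged and side-specific nodes are counted.

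**Formula.** With k nodes there are k(k − 1)/2 pairs. Pairs that include the corona radiata are all pairs minus those left when its node or nodes are dropped.

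| Node scheme | All pairs | Pairs without corona radiata | Pairs with it | Share |
|---|---|---|---|---|
| 7 merged nodes | 7 × 6/2 = 21 | 6 × 5/2 = 15 | 6 | 6/21 = 28.6% |
| 14 nodes, all bilateral | 14 × 13/2 = 91 | 12 × 11/2 = 66 | 25 | 25/91 = 27.5% |
| 13 nodes, bilateral with one midline SMA | 13 × 12/2 = 78 | 11 × 10/2 = 55 | 23 | 23/78 = 29.5% |

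The share hardly moves with the node scheme: between 27.5% and 29.5%.

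**Frontal cortex, counted separately.** If the frontal cortex mask contained M1 and SMA, two more of the 21 pairs would be affected (frontal–M1 and frontal–SMA), giving 8/21 = 38.1%. With 14 nodes and same-side overlap there would be four more, giving 29/91 = 31.9%. Counting all eight frontal–M1 and frontal–SMA pairs gives 33/91 = 36.3%. These figures depend on an overlap that the article does not state, so they are not part of the finding.

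**After the change.** With the corona radiata out of the pair set, 15 pairs remain (66 if bilateral), and none of them has a white-matter node.

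**The case against.** Several counter-arguments have weight.

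- **An article leaves mask detail to the full protocol.** Section 2.8 says that masks will be version-controlled, so they exist elsewhere. This answers the question of the frontal cortex boundary, but not the main point. The article positively places the corona radiata in the set for both kinds of connectivity, and no mask file cures that while the region remains a node.
- **The measures are defined.** A white-matter BOLD correlation and the FA along streamlines that reach a white-matter mask are both computable, and FA and MD in the corona radiata are legitimate. This stands. The fault lies in what the numbers can be taken to mean, so a reader who concluded that these pairs are invalid measurements would go too far.
- **Randomisation protects the comparison.** The same ROI definition applies in both arms and at both scans, and the outcomes are changes over six weeks. This also stands: no directional bias between arms is shown.
- **Coupling is not a listed primary outcome.** Section 2.7.2 lists ALFF, ReHo, FC, FA and MD; only the Discussion calls the coupling tests confirmatory. True, but FC is on that list, and 2.11.1 makes the seven regions primary for FC as well. ALFF, ReHo and the voxel-wise analyses do not depend on ROI pairs and are untouched.

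Two stronger readings are tempting. One is that over a third of the pairs are affected because frontal cortex contains M1 and SMA. The article does not support this: the Discussion lists frontal regions apart from M1 and SMA, and the masks are not shown. The label is loose, which is all that can be said. The other is that the ROI list contradicts section 2.7.2. There the text reads "Seed-based analysis (e.g., bilateral insula, M1 orofacial area, SMA"), which is offered as examples, and all three regions belong to the seven.

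**Conclusion.** The point holds in a limited form. The set that the article calls primary, and in the Discussion confirmatory, uses a region that the article itself calls white matter as a BOLD node and a tract endpoint. If all pairs are used, about 27% to 30% of them are affected: 6 of 21 with seven nodes, 25 of 91 with all nodes bilateral. For these pairs FC cannot be read as hub-to-hub connectivity, and tract FA comes partly from the node. They enter the coupling index, which the Discussion presents as its main mechanistic test. How far they shift that index, or the difference between arms, cannot be derived from the document. An overlap of frontal cortex with M1 and SMA is possible but not established.

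**What to change.** Before unblinding, issue a dated clarification with the same wording in 2.11.1 and the Discussion:

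1. Keep the corona radiata as a region for FA and MD only.
2. Remove it from the FC pairs and the coupling pairs, leaving six ROIs and 15 pairs (66 if every region is split by side). It still contributes to tract FA wherever a tract between two remaining hubs runs through it.
3. State that the frontal cortex mask excludes M1 and SMA voxels, so that the label cannot overlap them. Any named, non-overlapping parcel will do.

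The work is a change to masks and wording. The price is fewer pairs per patient for the coupling index, 15 in place of 21. Timing matters: section 2.15 says that at submission the data were blinded and no primary outcome analysis had been run, and 2.4 puts unblinding after the primary analyses. The change should be dated before those analyses begin; made later, it would look driven by the data.
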